## Discussion

3.

### Physical literacy and the intervention

3.1.

The PL concept holds promise to address individual's determinants for physically active lifestyles holistically. In this regard, the concept could contribute to the problem that the COVID-19 pandemic has negatively affected levels of and qualifications for adequate PA behaviors. However, although crucial documents in the area of health and policy [e.g., the Global Action Plan on Physical Activity 2018–2030 (15)] have suggested stakeholders to align practices with PL, not all countries acknowledge PL similarly and have facilitated the adoption of this concept by systematically promoting country-specific groundwork (e.g., through theoretical discussions or the development of assessment instruments) (34). This scholarly initiative bases on the assumption that also Germany lacks corresponding experiences with the PL idea (46) and that schools represent the appropriate setting to efficiently reach children along the socioeconomic spectrum.

The present study derives a theory-based PL intervention for children aged 8–11 years and uses the extracurricular time at primary schools to facilitate the child-centered concept outside the traditional compulsory atmosphere. The specificity of this intervention lies in the explicit theory-content links (70), the consideration of integrative principles between the PL domains as well as the consecutive advancements across the two pilot studies. The initial pilot cycles account for potential risks coming up during the preparation of the main study and will be embedded into a mixed-methods design that covers the perspective of both the intervention deliverers and recipients (i.e., children). In the main study, the intervention is finally tested in a controlled design to gather information about its effectiveness.

### Limitations

3.2.

However, the study has the limitation that the logistic situation (i.e., trainer qualification, infrastructure) does not permit to include water-based activities, although aquatic experiences represent an important aspect of PL development (105, 106). Furthermore, the children cannot be randomly assigned to the intervention and control condition. In this context, classes constitute the level of organization, thus making randomizations on the individual level impossible. Unfortunately, we could not realize a cluster-randomized controlled design for two reasons. First, we anticipate a too low overall number of participating classes to ensure a balanced distribution of hypothetical confounders (in the sense of a “robust” randomization). Second, classes were nested in schools and organizational processes within the schools (e.g., the health agent or director of a school), i.e., from third persons outside the academic teams, make it necessary to prescribe the order of classes involved. Nevertheless, the controlled design will allow to give recommendations regarding the potential application of the intervention for children in Germany. In the long term, such evidence-supported interventions can inform national and international practices with a holistic claim toward PA.

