**Figure 1 F1:**
[figure not shown]
Study design.

After the completion of the two pilot studies, we will follow up with the main study. The main study will more rigorously examine the effectiveness of the final PL intervention in a controlled design. In each school, an even number of classes of one grade level will participate in the study. Half of the classes will be assigned to the intervention condition, which will pass regular half-year education in primary school plus a weekly PL intervention. In contrast, the other half of the classes will be assigned to the control condition, which will undergo only regular half-year education in primary school without the additional PL intervention (see Figure 1). Randomization cannot be fully realized as pragmatic reasons co-influence the assignment to the different intervention arms (57). The main study, which also includes two measurement time points (e.g., pre and post), will take place between September 2023 and February 2024. In summary, the research design with two pilot cycles (51) accounts for potential pitfalls (e.g., revision of PL content) toward a sound examination of the effectiveness of the PL intervention. The final reporting of study will adhere to the recent physical literacy interventions reporting template suggesting a total of 14 items (58). The ethics committee of the University of Oldenburg, Germany, has approved the conduction of the study (sign Drs.EK/2022/057).

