The focus of the PL interventions will be placed on pupils of the third or fourth grade, wherein the class will serve as the level for the assignment to study conditions. Accordingly, the present study will address children aged between 8 and 11 years within the trial and analyses. Furthermore, children and their legal guardians will have to provide informed consent to study participation. In line with the inclusive potential of PL (69), children with diagnosed special needs will be invited to join the intervention (as long as they can participate in regular physical education) and evaluation. Nevertheless, they will be excluded from the analysis for psychometric reasons.

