### Sample size

2.6.

We performed sample size calculations with the software G*Power version 3.1 (94). For the uncontrolled *pilot study* adopting a pre-post character, we expect a minimum effect size of *d_z_* = 0.40 while considering the influence of general development effects. In this case, the minimum sample size to be acquired through one-sided, paired sample *t* tests (statistical power ≥ 80% and one-sided *p* < .05) will be *n* = 41. Assuming a conservative dropout rate of 25% (as usual for this target group, see (14, 95), an initial sample of *n* = 55 children will be recruited. Given an average number of approximately 20 pupils per class, we will include three to four classes for the pilot study.

For the subsequent main study in a control group design, we base a significant effect on time-group interactions of repeated multivariate analyses of variance (MANOVA). Aiming to control for general development effects through the involvement of a control arm, we set a smaller effect size of *d* = 0.30 (corresponding to *f* = 0.15) in this part of the study. Power calculations with an adjusted significance level (five PL outcomes:.05/5) of *p* ≤ .01 resulted in a required sample size of *n* = 134 children across the two study conditions (autoregressive pre-post correlation *r_t_* = 0.50, statistical power ≥ 80%). A total of nine to ten classes (dropout corrected *n* = 179 children) should initially participate in the main study.

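### Too few classes is not a valid reason against randomising; the within-school layout can carry a draw wherever a school can accept one

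*Protocol article*

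**What the plan says.** The class is the unit of assignment (section 2.2: "wherein the class will serve as the level for the assignment to study conditions"). Section 2.1 sets a blocked layout: "In each school, an even number of classes of one grade level will participate in the study", and "Half of the classes will be assigned to the intervention condition". It then says: "Randomization cannot be fully realized as pragmatic reasons co-influence the assignment to the different intervention arms".

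Section 3.2 lists the lack of randomisation as a limitation and gives two reasons for not using a cluster-randomised design:

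1. "we anticipate a too low overall number of participating classes to ensure a balanced distribution of hypothetical confounders".
2. Classes sit within schools, and organisational processes there, coming "from third persons outside the academic teams, make it necessary to prescribe the order of classes involved". A school director and a health agent are the examples given.

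On size, section 2.6 states: "A total of nine to ten classes (dropout corrected *n* = 179 children) should initially participate in the main study". Section 2.7.2 makes the time-by-group interaction of a repeated MANOVA the main test, and names the TREND statement for non-randomised designs as the framework.

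**The concern.** The first reason treats a small number of clusters as an argument for non-random assignment. A small number does limit how well a draw can balance confounders. But the alternative the plan uses works with the same classes, so it has the same chance imbalance. It also opens a route for systematic selection, because people who know the classes can influence which of them receive the programme.

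If that influence is related to how a class would have developed anyway, the difference goes into the time-by-group interaction. Subtracting baseline does not remove a difference in development. Entering class as a covariate cannot separate it from the programme effect either, because each class belongs to one arm only. If schools share a criterion, the bias has the same direction in each and does not average out over schools. According to the Abstract, the results are to decide on scale-up.

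**Working it through.** **Step 1. Reproduce the planned size.** Inputs from section 2.6: f = 0.15, alpha = 0.01, pre-post correlation 0.50, power at least 80%. For the interaction with two groups and two times (m = 2):

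- lambda = f² × N × m / (1 − r) = 0.0225 × 134 × 2 / 0.50 = 12.06, with 1 and 132 degrees of freedom.
- Power at N = 134 is 0.803, so the plan's figure reproduces.
- Dropout: 134 / 0.75 = 178.7, that is 179 children. The 25% is stated for the pilot study, and the step from 134 to 179 implies the same rate.
- Classes: 179 / 20 = 8.95. Even numbers per school force an even total. Eight classes give 8 × 20 = 160, below 179, so the layout needs ten.

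**Step 2. Can this layout carry a draw?** The number of 1:1 allocations is the product over schools of C(k, k/2), where k is the number of classes in the school.

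| Classes per school | Total | Allocations |
|---|---|---|
| 2+2+2+2+2 | 10 | 2⁵ = 32 |
| 4+2+2+2 | 10 | 6 × 2 × 2 × 2 = 48 |
| 4+4+2 | 10 | 6 × 6 × 2 = 72 |
| 6+4 | 10 | 20 × 6 = 120 |

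A draw is possible as far as numbers go, it balances school and grade by construction, and N stays at 134 (179 recruited).

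**Step 3. What the low count really limits.** With five pairs the smallest one-sided randomisation p-value is 1/32 = 0.031. Few classes therefore restrict class-level inference and chance balance, under either way of assigning.

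**Step 4. Illustration of possible selection bias.** The plan gives neither a class ICC nor any measure of selection, so both are assumptions. With r = 0.50 the variance of change is 2(1 − 0.50) = 1 times the outcome variance, so one SD unit serves for both. Let ICC be the class share of the variance of change. Let rho be the correlation between whatever drives the assignment and how the class would develop without the programme. With two classes per school and no true effect:

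expected spurious difference = rho × (2/√π) × √ICC = rho × 1.128 × √ICC

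| rho | ICC 0.02 | ICC 0.05 | ICC 0.10 |
|---|---|---|---|
| 0 (for example, decided by hall slots) | 0 | 0 | 0 |
| 0.25 | 0.04 | 0.06 | 0.09 |
| 0.5 | 0.08 | 0.13 | 0.18 |
| 1.0 | 0.16 | 0.25 | 0.36 |

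A negative rho, such as choosing the class thought to need the programme most, may reverse the sign and hide a real effect. At rho = 0.5 the values are 0.080/0.30 = 27% to 0.178/0.30 = 59% of the planned d. Simulation of the rho = 1 case gave 0.25 at ICC 0.05 and 0.36 at ICC 0.10, in agreement.

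**Step 5. What a draw leaves.** The expected difference under a draw is 0, but for five pairs the class component still varies with SD √(2 × ICC / 5): 0.09, 0.14 and 0.20 at the three ICCs.

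**The case against.** The strongest defence is the second reason. If the school organisation fixes which class can come when, a draw may be impossible whatever the class count. This stands: no section says how many schools could accept either result, and it may be none.

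A reader might infer that school staff choose which class gets the programme, and favour the keener or easier one. The text does not say so. It says that pragmatic reasons have a share in assignment and that school-side persons make a set order necessary. Section 2.2 speaks of hall slots, free times and material, and assignment driven by such things need not relate to class development. Staff influence is possible; a criterion linked to the outcome is not shown.

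A reader might also infer that a free draw is available and would remove the bias. The layout permits one, but feasibility in the schools is not established. A draw removes allocation bias only in expectation and only where it is made.

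Two smaller points stand in part. Baseline domain scores, sport club membership, recreational sport and travel to school are recorded and could capture some selection, though not unmeasured differences in development. The lack of randomisation is also openly disclosed. Disclosure keeps readers from being misled, but it does not make the first reason valid.

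**Conclusion.** The first reason in section 3.2 is not valid and should not support the choice of a non-random design. The class count does not prevent a within-school draw: ten classes give at least 32 allocations at no change in N. Whether the second reason does prevent it, and in how many schools, cannot be told from the document.

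The size of any bias is not known. Under assumed class ICCs of 0.02 to 0.10 it runs from 0 (assignment unrelated to development) to 0.08 to 0.18 SD at a selection correlation of 0.5, against the planned d = 0.30, with either sign possible. These figures show a mechanism and do not estimate the bias in this study. It would be tempting to turn them into a false-positive rate from a simple paired comparison of classes at 5%. That would not describe the planned child-level MANOVA at p ≤ .01, so no such rate is given.

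**What to change.** In section 3.2, delete the low number of classes as a reason against randomisation and keep the organisational reason.

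In section 2.1, replace the assignment rule with wording such as: *Each school nominates an even number of classes of one grade. Where the school confirms beforehand that any of these classes could take the programme, the research team draws by lot, within the school, which half receive it. Elsewhere, who assigned each class and why is recorded before the pre-test, and the school is treated as non-randomised. The result for the drawn schools is reported beside the overall result.*

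The cost is a change of wording, one lot per willing school and a short record for the others. No classes, staff or measurements are added. The downside is that some schools lose the choice of class and the study may be only partly randomised. The overall result would still carry any selection from the non-drawn schools, and the drawn-school result may rest on few pairs.

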### Dissemination aspects of this study

3.3.

In case of a successful main study with results justifying a further use of the PL intervention, the development of a dissemination strategy may come into play. Indeed, the present project has reserved personal, temporal, and financial resources for four months to potentially prepare a dissemination strategy that may flow into a follow-up study. For instance, teachers could be systematically trained for more sustainable, internal delivery in participating schools, potentially paralleled by an entire whole school approach permeating the entire institution (107, 108). A dissemination could also aim at reaching a wider target group by performing a so-called “scale-up” of the intervention (103, 104). Of course, the type of the scale-up depends on the results and their interpretations but also on pragmatic arguments and the development of the scholarly landscape on PL. For instance, a scale-up on the *geographical level* would implicate that also locations outside the city state of Bremen, Germany, could be addressed to reach children in other areas. Adopting the character of a *sectorial scale-up*, the successful intervention could be adapted and used in other settings, such as sport clubs or community-based work. As a further alternative, a scale-up on the *ontogenetic/chronological level* could mean that individuals of another age could benefit from a similar or slightly adapted PL intervention. In any case, dissemination strategies should also test whether the adapted PL intervention then also works in other settings, in other regions, or in individuals of another age.

## Data Availability

The original contributions presented in the study are included in the article/**Supplementary Material**, further inquiries can be directed to the corresponding author.
